### Study sample

#### General dental practices

The study will include 40 general dental practices: 20 practices in the intervention group and 20 in the control group. A convenience sampling method will be used to recruit dental practices for the intervention group. OHPs will be informed about the study at dental conferences and in-service training in The Netherlands, after which they are encouraged to voluntarily apply for participation. Practices will be eligible to participate if they have employed a certified dental therapist who is able to carry out and coordinate the study within their practice. Referral practices for paediatric dental care will be excluded from participation. All practices that apply will receive an information letter describing the procedures of the study, after which they will be asked to confirm their participation. Practices in both rural and urban regions will be included in the study.

For each participating dental practice in the intervention group, a matching control practice will be selected based on two factors: similar size of the patient population, with a maximum deviation in size of 500 registered patients; and same socioeconomic status (SES) of the region, as classified by the Dutch Central Bureau of Statistics on a scale from 1 (lowest SES) to 7 (highest SES) [23]. The size of the patient population gives an indication of the characteristics of a dental practice (e.g. solo or large group practice), and the SES of the region is indicative of the population’s (oral) health, with higher caries levels being reported in low SES regions [24]. Selected practices will be approached by e-mail, containing the information letter, and by telephone. As an incentive for participation, control practices will be offered training in the intervention method after the study is completed.

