#### Children and their parent(s)

Each dental practice, both in the intervention and control group, will recruit a sample of at least ten 3 to 4-year-old children from their own patient population for inclusion in the study, using a simple random sampling method. Eligible children will be listed from the patient registry and given a random number by the coordinating dental therapist, using the website http://random.org. Subjects will be approached in numerical order until at least ten subjects are included. In cases of twins, only one child of the family will be selected. Children will be eligible to participate if they are healthy (ASA classification I) and between 36 and 59 months old at the time of inclusion. Exclusion criteria are:
Children with a physical or mental disability,Children with a high caries activity (decayed, missing and filled teeth (dmft) ≥ 4), based on the patient dental record,Children with hypomineralised second primary molars,Children (or siblings of the child) who have been receiving treatment at a referral practice for paediatric dental care,Children of parents who do not speak and understand the Dutch language.

Three to 4-year-olds are selected for two reasons. First, the restriction of the age group reduces variation in dental caries levels, allowing better comparison of the intervention’s effect. Second, children are preferably targeted from a young age when oral health behaviours are still shaped and more amendable to change. However, in The Netherlands only 35% of two-year-olds are visiting the dentist, which increases to 95% when children reach the age of four [25]. Therefore, the choice was made to include 3 to 4-year-old children, increasing the number of young children that can be reached. Parents will be informed about the study aim and procedures, privacy and confidentiality regulations and their rights to withdraw at any time using an information letter (Additional file 1). Prior to participation, written informed consent will be obtained from the parents by the dental therapist.

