### Outcome measures

The primary outcome of this trial, children’s dental caries experience after 24 months, are measured at T2. Secondary outcomes, namely ^1)^ parents’ self-efficacy (confidence) in brushing their children’s teeth when experiencing barriers, ^2)^ tooth brushing frequency in children, and ^3)^ children’s dental plaque scores, are measured at T0.0, T1 and T2. The intervention is considered successful when a 25% reduction in dental caries experience is observed in the intervention group in comparison to the control group, which equals a reduction of 1.5 to 2.0 dmfs. Tooth brushing-related outcomes are assessed to provide additional information on the intervention’s effect and on the pathways by which the intervention might affect children’s caries experience. If one of more tooth brushing-related outcomes are significantly more favourable in the intervention group compared to the control group, but dental caries experience is not reduced by at least 25%, the intervention is not considered successful.

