#### Co-variates

Sociodemographic characteristics, including the child’s age, gender, parental education level, household income, family structure and ethnicity, will be collected using a questionnaire. The questionnaire also includes questions on other oral health behaviours, such as dietary factors, selected from the questionnaire from Pine et al. [32] (Additional file 2). These variables are collected because they are known moderators of the tooth brushing-related and clinical outcomes, and they therefore need to be adjusted for in the analyses. In addition, information will be extracted from dental records on the restorative and preventive treatments children received during the study, to allow to adjust for this in the analysis and interpretation of data.

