### Statistical analysis

All data will be coded with a unique ID, and data will be securely stored at the Department of Social Dentistry at ACTA. The analysis will be performed in STATA. Differences in the primary outcome (dmfs and the combined ICDAS scores ‘B and C’ and ‘A, B and C’) between children in the intervention and control group at T2 will be analysed using zero-inflated Poisson or negative binomial regression. Baseline differences in children’s dmft scores (obtained from dental records) will be taken into account.

Differences in the three tooth brushing-related outcomes between children in the intervention and control group at T1 and T2 will be analysed using ordered logistic or logistic regression (for tooth brushing frequency in children; either treated as a ordinal variable or dichotomous variable, depending on the distribution of responses), and linear or negative binomial regression (for parental self-efficacy scores and children’s plaque scores).

All analysis will be adjusted for clustering of observations within dental practices. In case of significant differences in co-variates (moderators) between the intervention and control group at baseline (T0), the analysis will be adjusted accordingly for these co-variates, or in case of sufficient power, a sub-group analysis will be performed. An intention-to-treat analysis will be conducted to account for participants that will be lost to follow-up. Statistical significance is set at α = 5%.

Qualitative data from the focus group interviews and telephone interviews will be processed using the Maximised Qualitative Data Analysis programme (Verbi-software MAXQDA). Conventional content analysis will be used to identify emergent themes and concepts related to the feasibility and acceptability of the intervention.

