A strength of this non-randomised cluster-controlled trial is the evaluation of the intervention’s impact on tooth brushing-related outcomes, as well as its clinical impact on children’s caries experience over a period of 24 months. Several process characteristics will also be assessed, such as the feasibility of the intervention as perceived by parents and OHPs, and information on implementation fidelity. This will provide insights that could be relevant for potential adaption and improvement of the intervention approach. Another strength is that the study will be conducted by OHPs in a real world clinical dental setting. The challenges and learnings that result from these real-setting experiences will be useful to facilitate future implementation. The participating dental practices will be located in both rural and urban regions, which benefits the generalisability of this study.

This study also has a few limitations that should be acknowledged. The method to recruit dental practices may cause selection bias. The study uses a convenience sample of dental practices in the intervention group, who are included based on voluntary application as opposed to randomisation. As a result, levels of engagement and motivation to provide preventive dental care may be higher in the intervention group. The generalisability of our study is further limited by excluding parents who do not understand the Dutch language and children with a very high caries activity (dmft ≥4 at the age of 3 years). Also, children who do not visit the dentist at the age of three and four will not be included in the study, which could potentially bias the sample towards more motivated parents and children. Furthermore, despite the use of validated questionnaires, parents may respond in a social desirable manner to questions related to self-efficacy and tooth brushing frequency. Lastly, there is a risk that dental therapists will drop out of the study. In this scenario, a colleague from the same dental practice will be requested and trained to collect follow-up data from the already included participants. The risk of contamination bias is expected to be low, given the clustered design of the trial, and the fact that control practices will not be informed about the practices that are in the intervention group and vice versa. Furthermore, control practices will not be able to provide the intervention without having received the supporting tools and training in methods and underlying theory.

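### The primary caries model does not name baseline tooth brushing or plaque and leaves further adjustment to baseline significance tests; prespecify both as covariates

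*Protocol article*

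**What the plan says.** The Statistical analysis section compares dmfs and combined ICDAS scores at T2 by zero-inflated Poisson or negative binomial regression, adjusted for clustering within practices. On baseline caries it says: "Baseline differences in children’s dmft scores (obtained from dental records) will be taken into account". Further adjustment is conditional: "In case of significant differences in co-variates (moderators) between the intervention and control group at baseline (T0), the analysis will be adjusted accordingly". A subgroup analysis is the alternative if power allows.

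The Co-variates section describes two questionnaire groups: "Sociodemographic characteristics, including the child’s age, gender, parental education level, household income, family structure and ethnicity", and then "The questionnaire also includes questions on other oral health behaviours, such as dietary factors". It adds treatments received during the study, taken from dental records. It names neither tooth brushing nor plaque.

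Both are nevertheless collected at baseline. Under Outcome measures, self-efficacy, brushing frequency and "children’s dental plaque scores, are measured at T0.0, T1 and T2". The article describes and models them as secondary outcomes only.

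On how the groups arise, intervention practices volunteer and "a matching control practice will be selected based on two factors": practice size and regional socioeconomic status. Within each practice, children are drawn "using a simple random sampling method". The Discussion concedes that "levels of engagement and motivation to provide preventive dental care may be higher in the intervention group".

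**The concern.** Without randomisation, the caries comparison depends on what is adjusted for. The protocol's own hypothesis (section on the ‘Uitblinkers’ intervention) runs from self-efficacy to twice-daily brushing, to less plaque, to less caries. Brushing and plaque measured before the intervention are therefore among the most direct baseline predictors of new caries over 24 months. They are not named for the primary model, while diet and sociodemographics are at least candidates.

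The term that is named is a limited substitute. Children with dmft of 4 or more are excluded, so it runs only from 0 to 3. It comes from practice records, and examiner training takes place only 23 months after the first inclusions. It describes past disease more than current brushing.

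The significance-triggered rule is a weak safeguard even for variables it covers. A baseline test measures evidence of imbalance, not the bias an imbalance causes, and at this sample size it will often miss a moderate one.

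Two features could create a baseline brushing imbalance, in opposite directions. Volunteer practices may be more prevention-minded, which could go with better-brushing families. Conversely, the section on development and procedure of the intervention excludes parents who cannot name a brushing barrier. That question belongs to the intervention interview, which control parents do not have. If the exclusion were applied only there, families with no brushing difficulty would leave the intervention group alone.

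**Working it through.** **What the document supplies.** It gives no baseline brushing distribution and no brushing–caries association, so there is no stated figure to reproduce for this point. The yardstick is the success threshold under Outcome measures: a 25% reduction, put at 1.5 to 2.0 dmfs. With the mean of 6.9 from the power calculation, 0.25 × 6.9 = 1.725 dmfs, which fits that range.

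**Step 1. Bias from an unadjusted brushing imbalance.** Let p0 and p1 be the proportions brushed at least twice daily at baseline in control and intervention, and R the ratio of dmfs in children brushed less often to dmfs in the others. With no intervention effect and no other adjustment,

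spurious reduction = 1 − [p1 + (1 − p1)R] / [p0 + (1 − p0)R].

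All values of p0, p1 and R are assumptions.

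| Control | Intervention | R = 1.5 | R = 2 |
|---|---|---|---|
| 65% | 70% | 1 − 1.150/1.175 = 2.1% | 1 − 1.30/1.35 = 3.7% |
| 65% | 75% | 1 − 1.125/1.175 = 4.3% | 1 − 1.25/1.35 = 7.4% |
| 65% | 85% | 1 − 1.075/1.175 = 8.5% | 1 − 1.15/1.35 = 14.8% |
| 80% | 70% | 1 − 1.15/1.10 = −4.5% | 1 − 1.30/1.20 = −8.3% |

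On a mean of 6.9, the first three rows span 6.9 × 0.021 = 0.15 dmfs to 6.9 × 0.148 = 1.02 dmfs. The last row shows the reverse imbalance, which masks an effect.

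**Step 2. Would the significance rule catch it?** Suppose brushing does count as a co-variate. Take 165 children per group (power calculation), a two-sided 5% test of two proportions, and the protocol's 15% clustering excess as a variance inflation, so the effective n is 165/1.15 = 143.5. With pooled proportion m = (p0 + p1)/2,

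chance flagged = Φ{[|p1 − p0| − 1.96√(2m(1 − m)/n)] / √([p0(1 − p0) + p1(1 − p1)]/n)}.

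| Control vs intervention | n = 165 | n = 143.5 |
|---|---|---|
| 75% vs 80% | 19% | 17% |
| 70% vs 80% | 56% | 50% |
| 65% vs 85% | 99% | 98% |

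For 70% versus 80% at n = 143.5: [0.10 − 1.96√(0.375/143.5)] / √(0.37/143.5) = (0.10 − 0.1002)/0.0508 ≈ 0, so Φ ≈ 0.50. The minimum of ten children in each of 20 practices gives 200 per group; the same formula then flags 70% versus 80% in 64% of cases, or 58% with the inflation (n = 200/1.15 = 173.9). A moderate imbalance is still missed in more than a third.

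So the rule would catch a 20-point gap, provided brushing is on its list, and is unreliable for gaps of 5 to 10 points. Those correspond to about 2% to 8% bias: for 70% versus 80%, 1 − 1.10/1.15 = 4.3% and 1 − 1.20/1.30 = 7.7%.

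**Step 3. Interaction with the success rule.** Bias combines with any true effect. At the extreme of the table, a true 15% reduction would appear as 1 − 0.85 × 0.852 = 27.6%, above the 25% threshold.

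**The case against.** **The covariate list belongs in the analysis plan.** A condensed article need not list every covariate, and an unseen plan may name these two. But this article does more than stay silent: it states one baseline term and a selection rule based on significance. That stated rule is what should change.

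**The text does not exclude brushing or plaque.** A reader might infer that baseline brushing and plaque can never enter the caries model. That reading rests on the word ‘other’ in the Co-variates section, which may only separate those items from the brushing questions described earlier. The list is open-ended and refers to an additional file that is not shown. The objection stands: the two are not named, which is different from being barred.

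**The direction of bias is not established.** A reader might also infer that better-brushing families in volunteer practices will be mistaken for an intervention effect. The document does not support this. The Discussion speaks of practices' motivation to provide preventive care, not of how families brush. Children are sampled at random within practices, controls are matched on size and regional status, and the no-barrier exclusion could push the other way. This stands too, though random sampling within practices does not remove differences between them.

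**Adjustment would not cure the confounding.** Brushing is parent-reported, the Discussion warns of socially desirable answers, and parents are not blinded. More preventive care during follow-up would not be captured by a baseline measure; the planned extraction of treatments addresses that separately. This also stands. Plaque is the firmer of the two, scored from photographs by examiners blind to group and time point.

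**The magnitudes are assumed.** They are, and even the largest stays below the 25% threshold on its own, before credit for dmft adjustment and matching.

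**Conclusion.** The point holds as an avoidable weakness in the stated primary analysis, not as a demonstrated bias. The model names a capped, record-based dmft score and leaves everything else to baseline significance tests, while two pre-intervention measures close to the outcome, already collected in both groups, are not named for it. The resulting bias could favour or mask the intervention. Its size rests wholly on assumed brushing gaps and dmfs ratios, and the upper end of the illustrated range requires a 20-point gap that no safeguard catches. It is worth correcting because allocation is not random and the correction is almost free.

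**What to change.** In the Statistical analysis section, prespecify T0.0 tooth brushing frequency (for example at least twice daily versus less) and T0.0 mean plaque score as covariates in the primary dmfs model, beside baseline caries and the clustering adjustment, whatever their baseline p-values. Report the intervention estimate with and without them, so that readers can see how far it moves.

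The cost is a change of wording, two extra model terms, and a stated method for a few missing T0.0 values, such as multiple imputation. No new data are needed.

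### Adjustment for the listed co-variates depends on a baseline significance test, although the Co-variates section requires it without condition and the trial is not randomised

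*Protocol article*

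**What the plan says.** The protocol article gives two rules for one set of variables.

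- **Co-variates.** The set is sociodemographic, "including the child’s age, gender, parental education level, household income, family structure and ethnicity, will be collected using a questionnaire", plus questionnaire items on diet and other oral health behaviours. The reason for collecting them is that "they are known moderators of the tooth brushing-related and clinical outcomes, and they therefore need to be adjusted for in the analyses". No baseline test is mentioned.
- **Statistical analysis.** "In case of significant differences in co-variates (moderators) between the intervention and control group at baseline (T0), the analysis will be adjusted accordingly" for those co-variates, "or in case of sufficient power, a sub-group analysis will be performed". Adjustment now depends on a significant difference, and a sub-group analysis may take its place.

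Three other statements bear on the point.

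- Under General dental practices, intervention practices apply voluntarily, and for each one "a matching control practice will be selected based on two factors": size of the patient population (within 500 registered patients) and regional SES class.
- The Discussion accepts that "levels of engagement and motivation to provide preventive dental care may be higher in the intervention group".
- Baseline caries has its own sentence in Statistical analysis. Baseline dmft differences are taken into account, with no significance condition.

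**The concern.** An analyst cannot follow both sections. If parental education differs between groups but not significantly, one section requires it in the model and the other leaves it out. This is not a detail left to a fuller plan, because the article itself states the rule, in two incompatible ways.

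The conditional rule is also the weaker one for this design. Without randomisation, systematic differences between the families of volunteer and matched practices are expected. How far a covariate distorts the dmfs comparison depends on its imbalance and on how strongly it predicts caries. A baseline test ignores the second and judges the first against sampling error. A strong predictor with a moderate, non-significant imbalance is therefore left out, and its bias stays in the primary estimate.

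The Outcome measures section declares success at a 25% reduction, put at 1.5 to 2.0 dmfs. A bias of a few tenths of a dmfs can carry an estimate across that line. The model would also be chosen from the data, so the nominal 5% error rate need not hold.

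**Working it through.** **Inputs from the Power calculation section:** 165 children per group, SD 6.2 dmfs, target difference 2 dmfs, 20% loss to follow-up, 15% excess for clustering, α = 5%.

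**The plan's own figure.** The normal formula n = 2(z_α + z_β)² × 6.2² / 2² gives 119 per group one-sided and 151 two-sided. One-sided, 119 × 1.20 × 1.15 = 164.2, hence 165 per group and 330 in total. The stated number is thus reproduced with a multiplicative 1.15 (two-sided, the same steps give 209 per group). I therefore use 1.15 as the design effect below.

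**Effective size at baseline:** 165 / 1.15 = 143.5 per group.

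**Step 1: what the baseline test can detect (two-sided 5%).**
- Smallest significant standardised difference: 1.96 × √(2/143.5) = 0.23 SD.
- True 0.2 SD imbalance: z = 0.2 / √(2/143.5) = 1.69, so it is missed with probability 0.605. At 0.15, 0.25 and 0.3 SD the probabilities are 0.75, 0.44 and 0.28.
- Binary covariate, assumed 30% versus 40%: SE = √(2 × 0.35 × 0.65 / 143.5) = 0.0563 and z = 0.10 / 0.0563 = 1.78. Power is 0.43, so it is missed with probability 0.57.
- With no clustering allowance at all (n = 165), z = 1.90 and power is still only 0.48.
- For 30% versus 35%, power is about 0.15.

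**Step 2: bias left by the screen, one confounder.** Assumption: the low-education group has 4 more dmfs (0.65 of the 6.2 SD). If nobody ever adjusted, the bias would be 0.10 × 4 = 0.4 dmfs. Under the stated rule, however, only trials with a non-significant observed difference stay unadjusted, and those have smaller realised imbalances:

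- E[difference | non-significant] = SE × {z + [φ(a) − φ(b)] / [Φ(b) − Φ(a)]}, with a = −1.96 − 1.78 and b = 1.96 − 1.78.
- = 0.0563 × (1.776 − 0.684) = 0.061, or 6.1 percentage points.
- Bias in those trials: 0.061 × 4 = 0.25 dmfs.
- Average over all trials: 0.57 × 0.25 = 0.14 dmfs, and 0.14 / 2 = 7% of the target.
- The bias scales with the assumed effect: at 2 dmfs instead of 4, the average is 0.07 dmfs.

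**Step 3: several confounders.** Simulation with no true effect: 4,000 runs per scenario, 115 effective children per group (165 × 0.8 / 1.15 = 114.8), a linear model with SD 6.2, independent covariates all shifted in the same direction, and no baseline caries term. Shifts and correlations are assumptions. Ranges cover shifts of 0.15, 0.2 and 0.25 SD.

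| Covariates | Correlation with dmfs | Mean bias, screened (dmfs) | Type I error, screened | Type I error, always adjusted |
|---|---|---|---|---|
| 1 | 0.3 | 0.14–0.15 | 5.2–6.1% | 5.0–5.6% |
| 3 | 0.3 | 0.45–0.48 | 8.6–8.7% | 5.1–5.2% |
| 5 | 0.2 | 0.49–0.54 | 8.9–9.8% | 5.1–5.6% |

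With fixed adjustment the mean bias was between −0.01 and 0.02 dmfs in every scenario.

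**The case against.** The best defence is that the trial does not depend on this rule alone, and that the harm from a single covariate is small. Much of that stands.

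- **Other protection exists.** A reader might infer that confounding in general goes uncorrected. The documents do not support that. Baseline dmft is taken into account without a test. Controls are matched on practice size and regional SES. Eligibility is restricted by age (36 to 59 months), health, baseline dmft below 4, referral history and language. The baseline caries term would also absorb part of any education or income effect, so the figures above lean high on that count. It need not absorb the part that acts on new caries during the 24 months.
- **The 0.4 dmfs figure.** A reader might pair the full 0.4 dmfs (20% of the target) with the 57% of trials that stay unadjusted. That is wrong, because trials failing the screen have smaller realised imbalance. The right figures are about 0.25 dmfs in those trials and 0.14 dmfs on average.
- **Sub-groups.** It would be wrong to say that a sub-group analysis removes no confounding: comparing groups within strata of a covariate does remove confounding by that covariate. The valid criticism is narrower. It yields no single adjusted primary estimate, it addresses effect modification, and the sufficient-power condition leaves the choice open.
- **Matching.** One might infer that the rule could never select the matching factors. Regional SES is matched on class, but practice size may differ by up to 500 patients, and practices recruit at least ten children rather than a fixed number. Any loss there is mainly of precision.
- **Motivation.** The higher engagement admitted in the Discussion is not among the collected covariates, so no adjustment rule for those covariates addresses it.

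What the defence does not answer is the contradiction between the two sections, or the fact that the test misses moderate imbalances more often than it finds them.

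**Conclusion.** The point holds in this limited form. The two sections contradict each other on whether the listed co-variates are adjusted for, and the significance-triggered version is a poor rule for a non-randomised comparison.

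The detection figures (43% for 30% versus 40%; about 60% of 0.2 SD imbalances missed) rest on the plan's 165 per group, its 15% allowance read as a design effect, and assumed imbalances. The cost is modest for one confounder: about 0.14 dmfs on average, 7% of the target, with type I error close to nominal. It becomes material, about 0.5 dmfs and 9–10% type I error, only if several covariates shift in the same direction. That is plausible for socioeconomic variables, but it is an assumption and nothing in the documents establishes it. The sizes of the confounder effects are likewise assumed. The rule therefore can leave avoidable bias in the primary estimate; the documents do not show that it will.

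**What to change.** Reconcile the two sections by replacing the conditional sentence in Statistical analysis with a fixed rule, for example:

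> The primary model includes, whatever the baseline comparison shows, baseline caries experience from the dental record, child age, gender, parental education, household income, family structure, ethnicity and the dietary items collected at baseline. Treatments received during the study are not part of this set. Sub-group analyses are exploratory, use interaction terms, and do not replace adjustment.

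The significance trigger is deleted. Treatments received during follow-up, which the Co-variates section also mentions for adjustment, stay out because they arise after baseline and may be affected by the intervention. Regional SES class and practice size may be added as practice-level covariates. Matched-pair terms are not required: 20 pairs would cost 19 parameters.

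The cost is wording, since every variable is already collected and the sample size stays at 330. The price is some degrees of freedom in a count model with 40 practices and about 264 children after 20% loss (330 × 0.8), so categories should be kept coarse. A rule for missing covariate values is also needed. The change does not deal with unmeasured practice motivation, which stays a limitation as the Discussion already says.

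### The Co-variates section requires adjustment, but the Statistical analysis section adjusts only after a significant baseline test or substitutes a sub-group analysis, which can leave small-to-moderate confounding in a non-randomised comparison

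*Protocol article*

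**What the plan says.** The Co-variates section lists what is gathered: "Sociodemographic characteristics, including the child’s age, gender, parental education level, household income, family structure and ethnicity, will be collected using a questionnaire". It adds other oral health behaviours, such as diet, from the same questionnaire. The reason given is that "they are known moderators of the tooth brushing-related and clinical outcomes, and they therefore need to be adjusted for in the analyses". No condition is attached.

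The Statistical analysis section sets a different rule: "In case of significant differences in co-variates (moderators) between the intervention and control group at baseline (T0), the analysis will be adjusted accordingly". The same sentence then offers a second route, which would stand in place of adjustment: "or in case of sufficient power, a sub-group analysis will be performed". Baseline caries has its own sentence, with no significance condition: "Baseline differences in children’s dmft scores (obtained from dental records) will be taken into account".

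Two design features bear on this. The Discussion describes the intervention practices as ones "who are included based on voluntary application as opposed to randomisation". The section on general dental practices says that "a matching control practice will be selected based on two factors: similar size of the patient population", the second factor being the socioeconomic status of the region. Nothing is matched at the level of the child or family.

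**The concern.** An analyst cannot follow both rules. If parental education differs between arms but the test is not significant, one section requires adjustment and the other does not provide for it.

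Of the two, the conditional rule is the weaker. In a randomised trial, baseline differences arise by chance. Here the arms are formed by self-selection, and the Discussion itself acknowledges possible selection bias. A non-significant test does not show balance. It shows only that the difference was small relative to its standard error, and that depends on the number of children and practices. Bias depends on something else: the size of the imbalance multiplied by the strength of the covariate's link with caries. The test ignores the second factor. The rule also makes the primary model depend on the data, and it drops strong predictors that happen to be balanced, at some cost in precision.

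Sub-group analysis does not replace adjustment. It gives separate estimates within levels of one variable, leaves the other variables unadjusted, and does not yield a single adjusted primary estimate.

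**Working it through.** **Inputs from the protocol article.** 165 children per group and 15% excess for clustering (Power calculation); 20 practices per arm (General dental practices); at least ten children per practice, hence 20 × 10 = 200 per arm (Children and their parent(s)); α = 5% (Statistical analysis); success at a 25% reduction in caries experience (Outcome measures).

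**Assumed inputs.** The documents give no expected imbalance, no covariate effect and no intraclass correlation. I assume a two-sided test, read the 15% as a variance inflation of 1.15, take low parental education as the covariate with 30% in the intervention arm and 35% to 50% in the control arm, and let low education multiply dmfs by 1.5, 2 or 3. The plan has no figure of its own to reproduce on this point.

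**Step 1: how often the baseline test misses the imbalance.**
Effective n = 165/1.15 = 143.5 per arm. SE = √[(p₁(1−p₁) + p₂(1−p₂))/143.5]. Miss probability = Φ(1.96 − |p₂ − p₁|/SE).

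| Low education | SE | Difference/SE | Missed, 165 per arm |
|---|---|---|---|
| 30 v 35% | 0.0552 | 0.91 | 85% |
| 30 v 40% | 0.0560 | 1.79 | 57% |
| 30 v 45% | 0.0565 | 2.66 | 24% |
| 30 v 50% | 0.0566 | 3.53 | 6% |

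At 200 per arm, effective n = 200/1.15 = 173.9. For 30 v 40% the SE is 0.0509, the ratio is 1.97, and the miss rate is 50%.

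For a continuous covariate at 165 per arm with the same allowance, the miss rates are 87% at 0.10 SD, 60% at 0.20 SD, 28% at 0.30 SD and 8% at 0.40 SD. The 50% point is 0.23 SD. It moves to 0.26 SD and 0.30 SD at assumed intraclass correlations of 0.05 and 0.10 with ten children per practice.

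**Step 2: the bias if 30 v 40% is present and left unadjusted, with no treatment effect.**
Ratio of means = (0.3R + 0.7)/(0.4R + 0.6), where R is the multiplier on dmfs.
- R = 1.5: 1.15/1.20 = 0.958, a spurious 4% reduction.
- R = 2: 1.30/1.40 = 0.929, a 7% reduction.
- R = 3: 1.60/1.80 = 0.889, an 11% reduction.

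**Step 3: the average under the plan's rule.** The test picks up the larger realised imbalances, so the average bias is smaller than in Step 2. With a true difference/SE of 1.786, its mean given non-significance is 1.786 − φ(0.174)/Φ(0.174) = 1.786 − 0.393/0.569 ≈ 1.10. That is a realised imbalance of 1.10 × 0.056 ≈ 6 percentage points, or about 32% v 38%.
- R = 2: 1.319/1.381 ≈ 0.955 when the test does not reject. Averaged with the remaining 43% of trials, which are adjusted and unbiased, this is 0.955^0.57 ≈ 0.974.
- R = 3: 1.639/1.761 ≈ 0.930, and 0.930^0.57 ≈ 0.960.

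A simulation (40 practices of 8 children, negative binomial counts with dispersion parameter 1.51, 800 trials per setting) gave 0.973 and 0.956 under the rule, against 0.999 and 0.996 when the covariate is always in the model. The average spurious reduction is thus about 3% to 4%.

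**Step 4: a check on another scale.** A separate simulation took a 0.2 SD imbalance, a covariate–outcome correlation of 0.5, 20 + 20 practices of 8 children and intraclass correlation 0.03. Bias was 0.103 SD with no adjustment, 0.044 SD under the significance rule and about 0.00 SD with adjustment always made. Type I error was 12.4%, 6.0% and 5.1%. At the plan's SD of 6.2, 0.044 SD is 0.27 dmfs, against the 2 dmfs that the trial is sized to detect.

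**The case against.** It can be argued that the two sections do not conflict: the first explains why the variables are collected, and the second says how they are used. On that reading the contradiction becomes loose wording, but the operative rule is then the weaker one, so the need for change remains.

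The stronger objections concern size, and they largely stand.

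- A reader might infer that real confounders will be left out more often than not. The documents do not support this. It is true only for imbalances below roughly 0.2 to 0.3 SD. At 0.40 SD, or at 30 v 50%, the rule would miss the covariate only 8% or 6% of the time. At the 200 per arm implied by the recruitment minimum, 30 v 40% is an even chance.
- A reader might also take the 4% to 11% as the bias of the planned analysis. It is the bias when the full ten-point imbalance goes unadjusted. Averaged over trials, the rule costs 3% to 4%, and type I error rises only to about 6%.
- Baseline dmft is taken into account whatever any test shows, and practices are matched on size and regional socioeconomic status. Part of the education gradient at 24 months will already be present in baseline caries, so the figures above, which ignore both protections, are on the high side. Neither protection works on family circumstances directly: the matching is at practice level, and baseline dmft is read from records of 3- to 4-year-olds after excluding those with dmft of 4 or more.

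These points reduce the size of the concern. They do not justify the significance condition.

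**Conclusion.** The point holds in a limited form. The two sections need reconciling, and selecting confounders by a baseline significance test is unsound in a self-selected comparison. Because the article states this rule, it is not detail left to an analysis plan.

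The practical effect is leakage of small-to-moderate confounding. Under the assumed 30 v 40% imbalance and a multiplier of 2 to 3, a single covariate shifts the caries ratio by 3% to 4% on average, and by up to about 11% if the full imbalance is left in. The success threshold is 25%, so this one variable would not by itself produce a declared success. Several unadjusted family factors pointing the same way could add up, but the documents give no basis for sizing that. All magnitudes rest on assumed imbalances and covariate effects. The conclusion about the rule does not. The change should be made before the 24-month data are analysed; the concern does not undermine the design.

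**What to change.** In the Statistical analysis section, replace the significance condition with a fixed set entered in every outcome model whatever the baseline comparison shows: child age, gender, parental education, household income, family structure, ethnicity and a short, pre-named list of T0 dietary items, in addition to baseline dmft. Decide how sparse categories are collapsed before the analysts are unmasked. Report baseline differences descriptively. Delete sub-group analysis as a substitute for adjustment; any sub-group analysis should stand beside the adjusted primary analysis, not replace it. The Co-variates section can then stay as it is.

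The variables are already collected, so the change is to wording only. The cost is some extra parameters in a count model with 40 clusters, which is why the dietary list should be short, and a stated way of handling missing covariate values.
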